**11. SAFETY/ADVERSE EXPERIENCES/EVENTS**

**11.1 Adverse experience reporting**

The investigator must report all adverse experiences (AEs) that occur throughout the study according to the appropriate procedures listed below. In case the investigator becomes aware of any possibly Serious Adverse Event (SAE), including death, he must report this event by phone to the CRO and the local Ethic Committee within 24 hours of notification of this event.

**11.2 The intensity or severity of an AE is characterized as:**

- **Mild**: AE which is easily tolerated.
- **Moderate**: AE sufficiently discomforting to interfere with daily activity.
- **Severe**: AE that prevents normal daily activities.

**11.3 The relationship and Adverse Event to the study treatment is characterized as follows:**

| **TERM** | **DEFINITION** | **CLARIFICATION** |
| --- | --- | --- |
| **Unrelated** | This category applies to those adverse events that, after careful consideration, are clearly and incontrovertibly due to extraneous causes (disease, environment, *etc*.) |  |
| **Unlikely** | In general, this category can be considered applicable to those adverse events that, after careful medical consideration at the time they are evaluated, are judged to be unrelated to the TCV. | Ad adverse event may be considered unlikely to be related if or when two or more of the following are found:   - It does not follow a reasonable temporal sequence from the TCV; - It could readily have been produced by the subject’s clinical state, environmental, or toxic factors, or other modes of therapy administered to the subject; - It does not follow a known pattern of response to the TCV; - It does not reappear or worsen when the TCV is re-administered. |
| **Possibly** | This category applies to those adverse events for which, after careful medical consideration at the time they are evaluated, a connection with the TCV appears unlikely but cannot be ruled out with certainty. | An adverse event may be considered possibly related if or when two or more of the following are found:   - It follows a reasonable temporal sequence from the start of the TCV; - It could not be reasonable explained by the known characteristics of the subject’s clinical state, environmental or toxic factors or other modes of therapy administered to the subject; - It disappears or decreases on cessation of TCV. There are important exceptions when an adverse event does not disappear upon discontinuation of the TCV, yet therapy-relatedness clearly exists (*e.g.* bone marrow depression, fixed drug eruptions. - It follows a known pattern of response to the TCV. |

**11.4 Serious Adverse Events**

Definition: A Serious Adverse Event (SAE) is defined as any adverse experience occurring at any TCV injection:

- Results in death;
- Is life threatening;
- Requires inpatient hospitalization or prolongation of existing hospitalization;
- Results in a persistent or significant disability;
- Is a congenital anomaly/birth defect;

Medical judgment should be exercised in deciding whether expedited reporting is appropriate in other situations, such as important medical events that may not be immediately life-threatening, result in death, or result in hospitalization, but may jeopardize the patient and/or may require intervention to prevent on of the other outcomes listed in the definition above. These could also be considered as serious.

Any SAE, whether deemed TCV related or not, must be reported immediately to the EC and the CRO.

**12. Statistical Methodology**

A total of 30 patients equally randomized to treatment with T-Cell vaccination (TCV) 10-50x106 irradiated cells, (20 patients), or to placebo, (10 patients), are expected to be recruited into this double-blind, placebo controlled. The trail is planned for 4 injection of double-blind treatment. Since the recruitment phase will last for 20 months, two interim analyses are planned to be conducted utilizing 30% and 80% of the accumulated trail information.

**12.1 Randomization Procedure**

After a patient meets the eligibility criteria, he/she will be allocated to one of the 2 treatment groups, based on randomization procedure employing a 2:1 assignment ratio, and a scheme using blocks stratified by centers. The randomization scheme will be prepared by the Sponsor's Statistics & Data Management (S&DM) Department, using the SAS® random number procedure.

The randomization list and the seed used to generate it will be kept sealed in the fire-protected safe.

Once the enrollment of the patient is approved, the enrolling investigator will assign the patient an ID number (patient number) according to the chronological order in which patients are randomized. Patients dropping out from the study after randomization will not be replaced.

Any difficulties in providing TCV treatment to the patient, such as cells thawing problems, low cell number, lack of cell for the vaccination, errors in patient numbers or other anomalies, should be reported immediately to the LCTM who will notify the S&DM Department and other individuals for whom this information is relevant.

**12.2 Significance levels**

The overall significance level for this study will be 5% using two-tailed tests. The treatment effect of the oral glatiramer acetate will be tested for significance by performing two comparisons (contrasts) for each end-point: the group treated with TCV will be compared to placebo. Hochberg's step-up modification to Bonferroni's method will be used to maintain the experiment-wise type I error.

- The MRI Completers Cohort: Consists of all patients having both basline and termination visit scans
  1. **Comparability of Treatment Group at Baseline**

The two treatment groups will be compared for baseline characteristics in each of the above-mentioned cohorts. This analysis will include general medical history, physical examinations taken prior to trial treatment initiation, baseline laboratory data and baseline MS disease measures. The continuous variables will be examined using one-way analysis of variance or the Kruskall-Wallis test, when appropriate, and the categorical variables will be examined for differences between group using the chi-Square test or Fisher's Exact test, when appropriate.

**13. ETHICS**

**13.1 Informed Consent**

The principles of Informed Consent, according to ICH -GCP guidelines, will be followed. A subject should not enter a clinical study until he/she has been properly informed and has freely given his/her consent by signing and dating two (2) original copies of the Informed Consent Form prior to performing any study related procedures.

One original copy will be given to the subject and the second one will be maintained at the site, following the signature and dating by the investigator and/or witness (where appropriate).

A copy of the proposed consent form must be submitted to the Ethics Committee (EC), together with the protocol, for approval.

**13.2 Ethics Committee (EC)/Institutional Review Board (IRB)**

An Ethics Committee/ must approve the study in writing. A copy of the Approval from the EC/IRB and the hospital director’s approval letter, which also contains specific identification of the documents approved, must be received prior to site initiation.

Any amendments to the protocol or subsequent changes to the informed Consent as a result of changes to the protocol and/or investigator brochure must be approved by the EC/IRB and documentation of this approval. Records of the EC/IRB review and approval of all documents pertaining to this study must be kept on file by the investigator and are subject to Regulatory Authorities inspection during or after completion of the study. Unexpected and associated SAEs must also be reported to the EC.

Periodic status reports must be submitted to the EC as required, as well as notification of completion of the study and a final report where applicable.

**14. DOCUMENTATION**

**14.1 Site Documents Required for Initiation**

Prior to the initiation of the study, the following items must be received

1. A signed copy of the protocol, amendments, and notifications (if applicable);
2. EC Written approval for the Protocol, Amendments, Informed Consent, Patient Information Sheet (if applicable), Advertisements (if applicable),
3. The investigator’s curriculum vitae, as well as the curriculum vitae of any co-investigator(s);
4. A list of the persons involved with the study and their signatures;
5. Study site agreement(s);
6. EC Membership list and EC operation procedures
7. Health Regulatory approval.

**14.2 Additional Site Documents**

Prior to the initiation of the study, the following items will be prepared:

- Study Protocol
- Investigator’s Brochure;
- Case Report Forms;
- Study Manual (Protocol SOPs for study specific procedures) and CRO’s SOPs.
- Model of Informed Consent;
- Central Laboratory Certification and Normal Ranges;
- Patients Information Leaflet;
- Insurance Certificate.

**14.3 Maintenance and Retention of Records**

It is the responsibility of the investigator to maintain a comprehensive and centralized filing system of all relevant documentation.

**14.3.1 Case Report Forms (CRF)**

CRFs for individual subjects will be provided by a professional CRF design company and or with cooperation with the CRO.CRFs are used to record study data and are an integral part of the study and subsequent reports. Therefore, the CRFs must be legible and complete. CRFs for this study will be maintained in a study binder and will be reported on a non-carbon (NCR) paper in the CRF (3 copies). One copy will be kept by the investigator and the two other copies will be collected by the study monitor. All forms should be complete using a dark ball point pen to ensure the data copies onto all CRF pages. Errors should be lined out *but not obliterated*, and the correction inserted, initialed, and dated by designated study personnel. Further data corrections will be performed on special “Data Clarification and Resolution Forms” (DCRF). Such DCRF will be dispatched to the investigator in case of erroneous or unclear data. After the correction is made by the investigator on the DCRF, a copy will be kept in the CRF file and the original given to the study monitor.

A CRF must be completed and signed by the relevant investigator (*i.e.*, neurological evaluation by the Examining Neurologist) for each subject enrolled, including those removed from the study for any reason. The reason for removal should be noted on the study conclusion CRF by the investigator for each subject.

CRFs must be kept current to reflect the subject’s status at each phase during the course of the study. Subjects are not to be identified on CRFs by name; appropriately coded identification and the subject’s initials must be used. The investigator must keep a separate log of the subjects’ names and addresses.

Source documents such as originals of laboratory and other test results are to be maintained separately from the CRF in order to allow data verification.

**14.4 Monitoring**

The CRO will be responsible for coordinating the activities of the study monitoring team, to ensure adherence to the study protocol, ICH-GCP guidelines and the CRO’s standard operating procedures. Study Monitors for this trial will be provided by the CRO. The monitors will act in compliance with ICH Guidelines.

**14.5 Quality Assurance Audits/Inspections**

**14.5.1 Good Clinical Practice**

The study described in this protocol will be carried out according to internationally accepted standards of Good Clinical Practice. All procedures not described in this protocol will be performed according to written standard Operating procedures unless otherwise justified.

**14.5.2 Quality Laboratory Standards**

Laboratory tests/evaluations of study described in this protocol will be conducted in accordance with quality laboratory standards and GLP (Good Laboratory Practice).

**14.5.3 Quality Assurance Program**

The study progress will be inspected according to the CRO’s QA inspection program. The final report will be audited to ensure that, as far as can reasonable be established, the methods described and the results reported accurately reflect the raw data generated during the study.

The purpose of such audit will be to determine whether or not the study is being conducted and monitored in compliance with recognized GCP guidelines or laws. An initial review will increase the likelihood that the study data and all other study documentation can withstand a subsequent inspection by any regulatory authority.

Such audits will be arranged within a reasonable time frame and agreed through the monitor.

**14.6 Maintaining the Study Blind**

The investigators (both the treating and examining neurologists, nurse coordinators, pharmacist and/or their staff at the study site), MRI personnel and the personnel involved in patient assessment, monitoring analysis and data management (excluding the personnel of the T-cell Process Laboratory), are blinded to the patient assignment. In order to ensure that information, which could potentially bias handling of data, is not disclosed, the following precautions are practiced:

- Randomization code envelopes are maintained by the PI in a protected file. No access will be permitted to those involved in patient data handling;
- Patients’ general medical evaluation will be assessed separately from their neurological assessment evaluation by two different neurologists. An examining neurologist will assess the patient’s neurological examination, unaware of the patient’s well being, and a testing neurologist will assess whether a patient experiences a relapse and will prescribe steroids or other concomitant medications as needed.

**15. STUDY PERSONNEL**

**15.1 At the Study Site**

At the study center the staff will consist of a minimum of two neurologists/physicians (a treating neurologist and an examining neurologist), MRI radiologist and technician, and a clinical coordinator (who can be a nurse or a neurologist). Treating neurologist will be the Principal Investigator.

**15.1.1 The Treating neurologist /Physician**

The treating neurologistwill be responsible for patient eligibility evaluation, the physical examination, the supervision of the TCV treatment regimen, the recording and treating of adverse experiences, the monitoring of safety assessments, including routine laboratory parameters, and coordinating MRI performance.

He will determine if a patient experiences a relapse and whether to treat his relapse or not.

**15.1.2 The Examining neurologist /Physician**

The examining neurologistwill be responsible for conduct the neurological examination (EDSS)

**NOTE: It is particularly important that the Treating Physician and the Examining Physician will not discuss safety issues together. The Examining Neurologist will not ask the patient any questions regarding his well being.**

**Both the Treating Physician and the patient will be informed of the importance of not discussing safety issues with the Examining Physician.**

**15.1.3 The MRI Radiologist and the MRI Technician**

The radiologist will be responsible for patient’s capability to undergo MRI scans, and evaluation of the MRI results. The MRI technician will perform of the MRI scans according to the protocol guidelines during the study, the preparation of the hardcopies and the electronic material for evaluation, as well as providing adequate storage and backups of the primary data at the site.

**15.1.4 The Clinical Coordinator**

A nurse or a physician will be responsible for patient scheduling and completing of all patients’ case reports forms.

S/He will instruct the patient concerning the protocol details of the TCV S/He will collect and forward blood samples and requests to the appropriate laboratories, will obtain and forward laboratory results and will assist all site study staff. S/He will also perform the additional clinical tests (10 Meter Walking Test, 9-Hole-peg test, PASAT cognition test.).

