**3.3 Studies in Humans.**

# Based on data accumulating in animal studies, an initial clinical trial was carried out in four patients with MS by Hafler and co-worker. Patients were inoculated with formaldehyde-fixed autologous T-cell clones isolated by phytohemaglutinin (PHA) stimulation from cerebrospinal fluid. The T-cell clones used for vaccination were chosen based upon their phenotype (CD4+), growth characterization and the expression of dominant, rearranged TCR genes, which represent the oligoclonal T-cell harboring in the brain compartment. The study revealed some interesting immunology findings regarding a general inhibition on T-cell stimulation via the CD2 pathway and increasing autologous mixed lymphocyte responses after vaccination (10).

Based on the successful treatment of EAE by T-cell vaccination in rodents and the potential pathological role of MBP autoreactive T-cells in MS, a phase I clinical trial was conducted by Zhang and co-workers (11).In this clinical trial, ten MS patients were vaccinated with irradiated autologous MBP-specific T-cell clones; MBP-reactive T-cell clones are generated by two-stage procedure within seven weeks. This study aimed to address feasibility toxicity, regulatory T-cell responses and potential changes in the frequency of circulation of MBP- reactive T-cells after vaccination. These preliminary clinical trials suggested that the vaccine clones were well-tolerated without adverse effects. T-cell vaccination was feasible and induced substantial anti-clonotypic T-cell responses to the vaccine clones. The data suggested that inoculation with irradiated MBP- reactive T-cell induces predominant CD8+ T-cell response that coincides reciprocally with a progressive decrease in the frequency of circulating MBP-reactive T-cells in all vaccinated patients. (11). After three inoculations spaced between two to four month, no circulating MBP-reactive T-cells were detected in treated patients, suggesting depletion of the target autoreactive T-cell (the injected cells). These effects were boosted by with each revaccination. Although no clear remission was observed, a series of neurological examinations suggested some clinical improvement regarding moderate reduction of the disease scores (EDSS) and the frequency of relapses in some relapsing remitting patients. Forty percent of the vaccinated patients were clinically stable during the vaccine.

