**Study Activities Flow Chart**

**STUDY TASK FLOW SHEET**

| Procedures | Screening | TCV Processing | Baseline | On Study Evaluation | | | | | |
| --- | --- | --- | --- | --- | --- | --- | --- | --- | --- |
|  | | | TC Injections | | | |  | | |
| *Visits* | 1 | 2-7* | 8 | 9 | 10 | 11 | 12 | 13 | 14 |
| *Months* | *-3* | -2 | 0 | 1 | 3 | 6 | 8 | 10 | 12 |
| Informed Consent | X |  |  |  |  |  |  |  |  |
| Eligibility Criteria | X |  |  |  |  |  |  |  |  |
| Medical History | X |  |  |  |  |  |  |  |  |
| Historical and  Concomitant Medications | X |  | X | X | X | X | X | X | X |
| Physical Examination | X |  |  |  |  |  |  |  | X |
| Neurological Exam and test | X |  | X | X | X | X | X | X | X |
| Laboratory Evaluation/Immunology |  |  | X |  |  | X |  |  | X |
| Serum β HCG | X |  |  |  |  |  |  |  | X |
| MRI-cerebral |  |  | X |  |  |  |  |  | X |
| Randomization |  |  | X |  |  |  |  |  |  |
| TCV |  |  | X | X | X | X |  |  |  |
| Adverse Experiences |  |  | X | X | X | X | X | X | X |

* Weekly visits for blood withdrawals for TCV preparation.

Preparation of T-cell Vaccination

Activity Flow Chart

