**7.6. Laboratory Evaluations**

All laboratory testing will be performed in our laboratories at the Hadassah University Hospital in Jerusalem.

-Serum chemistry

- - Glucose
  - Creatinine
  - Calcium
  - Total Bilirubin
  - Urea
  - AST (SGOT)
  - ALT (SGPT)
  - Cholesterol
  - Total protein
  - Albumin
  - Alkaline Phosphates
  - Phosphorous
  - Sodium
  - Potassium

-Hematology

- - Hemoglobin
  - Hematocrit
  - Red Blood Cells (RBC)
  - White Blood Cells + differential count
  - Platelets

-Urinalysis

- - Protein
  - Glucose
  - PH
  - Blood

-Serum β HCG for female patients (at screening visit and termination).

- Immunological (optional) follow up: Immunological follow-up of the patients will include the detection of:

- Frequency of the **specific auto-reactive** T-cells injectedone year from the last injection.
- Frequency of activated lymphocytes to recall antigens one year from the last injection.
- Frequency of **anti-myelin reactive** **lymphocytes** (**anti-clonotypic)** in the peripheral blood.
- Anti-idiotypic antibody levels in the peripheral blood.

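### The blinded coordinator who runs three secondary tests also handles all laboratory results, and nothing holds back optional T-cell immunology that could strongly indicate allocation

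*Protocol*

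**What the plan says.** **Who is blinded.** Section 14.6 covers "The investigators (both the treating and examining neurologists, nurse coordinators, pharmacist and/or their staff at the study site", together with MRI, assessment and data staff. The one group left out is given as "excluding the personnel of the T-cell Process Laboratory), are blinded to the patient assignment". The section then introduces its safeguards: "In order to ensure that information, which could potentially bias handling of data, is not disclosed, the following precautions are practiced". Two follow: the code envelopes are kept in a protected file, and general medical and neurological assessment are split between two neurologists.

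**What the coordinator does.** Under 15.1.4 the coordinator "will obtain and forward laboratory results and will assist all site study staff". The next sentence reads "S/He will also perform the additional clinical tests (10 Meter Walking Test, 9-Hole-peg test, PASAT cognition test". These three tests are secondary efficacy endpoints.

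**What counts as laboratory work.** The flow sheet has a single row, "Laboratory Evaluation/Immunology", marked at visits 8, 11 and 14 (months 0, 6 and 12). Section 7.6, on laboratory evaluations, contains the item "Immunological (optional) follow up: Immunological follow-up of the patients will include the detection of" and lists four assays. Section 9.1 places samples for immunological studies among the clinical laboratory studies at screening.

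**What the results may show.** Section 3.3 describes a ten-patient phase I trial with a "progressive decrease in the frequency of circulating MBP-reactive T-cells in all vaccinated patients".

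**The concern.** A blind can be lost without anyone opening an envelope, if a blinded person sees a measurement that the treatment itself moves. Here the treatment is meant to lower myelin-reactive T-cells and to raise a response against the injected cells, and those are quantities the immunology measures. Placebo is saline and contains no cells that could provoke such a response. Every patient must show myelin reactivity at screening to enter (9.1.1), so a later loss of reactivity would be noticeable.

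The person told to handle laboratory results is the one who times the walk, runs the peg test and administers the PASAT. The treating neurologist decides what is a relapse and whether to give steroids (7.3.2.2, 7.3.2.3, 15.1.1). The protocol takes indirect unblinding seriously elsewhere, since injection sites are bandaged before each examination (9.4, 9.5). This route is left open.

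**Working it through.** The protocol states no figure on this point, so there is none to reproduce. The check sets the passages side by side and then asks how informative a result could be.

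**1. Route.** The coordinator is blinded (14.6), handles laboratory results with no carve-out (15.1.4), and rates three secondary tests (15.1.4). Immunology is written as laboratory work in three places: the flow sheet, 7.6 and 9.1. Neither precaution in 14.6 concerns laboratory results.

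**2. Timing.** The places do not agree.

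- Flow sheet: the combined row is marked at months 0, 6 and 12.
- Section 5.3: optional immunology at inclusion, three-monthly, and at month 12.
- Section 9.4: only routine haematology, chemistry and urinalysis are named at month 6.
- Section 7.6: the injected-cell and recall-antigen assays come one year after the last injection, day 180 + 365 = 545, about month 18. The anti-clonotypic lymphocyte and anti-idiotypic antibody assays have no time.

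On the flow-sheet timing, a month-6 sample drawn before that day's injection follows three injections (days 1, 30 and 90). Section 3.3 reports no detectable MBP-reactive cells after three inoculations in one trial, and a decline after the second in a four-patient pilot. Visits at months 8, 10 and 12 follow a month-6 sample, which is 3 of the 6 post-baseline visits. On a three-monthly schedule exposure could begin earlier. On the month-18 timing it would come after the termination visit.

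**3. How much a result could reveal.** Let s be the share of vaccinated patients whose result reads as depleted, and f the share of placebo patients whose result does. The protocol gives no control-arm rate, so both are assumptions. Allocation is 20:10, so always guessing vaccine is right for 20/30 = 66.7%.

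- P(vaccine | depleted) = 2s / (2s + f)
- P(placebo | not depleted) = (1 − f) / [(1 − f) + 2(1 − s)]
- Share correct, calling depleted vaccine and the rest placebo = (2s + 1 − f) / 3

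| s | f | P(vaccine, depleted) | P(placebo, not depleted) | Share correct |
|---|---|---|---|---|
| 1.0 | 0.05 | 0.976 | 1.000 | 98.3% |
| 1.0 | 0.50 | 0.800 | 1.000 | 83.3% |
| 0.8 | 0.10 | 0.941 | 0.692 | 83.3% |
| 0.8 | 0.30 | 0.842 | 0.636 | 76.7% |
| 0.6 | 0.30 | 0.800 | 0.467 | 63.3% |
| 0.6 | 0.50 | 0.706 | 0.385 | 56.7% |

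For example, the first row is (2 × 1.0 + 1 − 0.05) / 3 = 0.983. In the last two rows a patient who is not depleted is still more likely to be on vaccine, so the best guess does not change and accuracy stays at 66.7%. With strong depletion the assay is highly informative. With weak depletion it does not improve the guess.

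**4. Outcomes reached.** The three coordinator tests are reached directly. Relapse and steroid decisions are reached only if results are forwarded to the treating neurologist. No passage sends laboratory results to the examining neurologist who scores the EDSS.

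**The case against.** The strongest reply is that the exposure may never occur. The immunology is optional (5.3, 7.6), the month-6 visit text does not name it, and two of its four assays are timed after the blinded period. No passage says that results go back to the site patient by patient during follow-up. Section 15.1.4 does not say to whom results are forwarded, and 15.1.1 names only routine laboratory parameters for the treating neurologist. Procedures not described are left to SOPs and a study manual (14.2, 14.5.1), which are not shown.

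The biological evidence is also thin. It comes from a ten-patient trial of MBP clones and an open pilot in four patients, with no control group described for either. Section 3.3 also reports loss of reactivity in most rather than all patients of another study, return of responses during exacerbation, no antibody response to vaccination, and contradictory findings on myelin reactivity in general.

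Relapses have some protection. They need an objective EDSS or functional-system change (7.3.2) scored by the examining neurologist, who is kept from safety discussion (15.1.2).

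All of this stands as a limit on size. It does not close the gap. Activated and anti-myelin-reactive lymphocytes are named tertiary outcomes, so the data are expected. The anti-clonotypic assay has no time that would place it after the blinded period. An optional assay with inconsistent timing needs a withholding rule that works whenever it is run.

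**Conclusion.** The point holds as a conditional one. The text routes laboratory results, which as written include optional immunology, through a blinded outcome rater, and nothing keeps results that may reveal the arm from the site until lock. It bites only if the assays are done and reported before lock. Then three secondary tests are exposed, at 3 of 6 post-baseline visits on the flow-sheet timing. Relapse and steroid decisions are exposed only through onward forwarding.

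A reader might infer more. One inference is that from month 6 site staff can see who was vaccinated. The documents do not support it: the month-6 timing rests on one combined flow-sheet row, and the cited evidence does not identify every patient. A second is that a count of unmasked patients, or a bias in relapse totals, can be given. It cannot. The protocol supplies no placebo-arm rate of apparent depletion. The relapse rate in 12.3 comes from relapsing-remitting trials, and its effect sizes are stated with reference to glatiramer acetate rather than this vaccine. A third is that the EDSS score is directly compromised, and no passage shows that.

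The accuracy range in the working rests on assumed values of s and f and only illustrates how informative a result might be. The change is worth making because it costs almost nothing.

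**What to change.** 1. In 15.1.4, limit the sentence on results to routine haematology, chemistry, urinalysis and beta-HCG.
2. In 14.6, add a third precaution: all post-baseline immunology results (reactive-cell frequencies, anti-clonotypic and anti-idiotypic responses) stay coded with the assay laboratory. They are not released to site staff, patients or monitors until the month-12 data of all patients are locked. Screening reactivity results, which decide eligibility before randomization, are unaffected.
3. Reconcile the immunology timing in 5.3, the flow sheet, 7.6 and 9.4, and give the flow sheet separate rows for routine laboratory tests and immunology.

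The cost is a few sentences of protocol text, with no extra staff or procedures and no loss of routine safety results. The small downside is that investigators see the immunology only after lock.
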